#### SP5: implementation and evaluation

SP5 provides guidance on IPS development, rooted in implementation theory, and evaluates the overall outcomes of the IMPLEMENT project. Both dedicated and generic models and frameworks of implementation theory are provided and tailored to each IPS in close collaboration with the relevant subproject. This process also includes a dedicated process evaluation for each IPS to assess its implementation effectiveness. Detailed information on the overall evaluation of IMPLEMENT is provided below (see step 3).

#### Additional project component: economic evaluation

This involves developing a cost reimbursement model for qOET by analysing current billing structures, resource requirements, and service scalability. Further, information derived from the questionnaire for cancer patients and stakeholders (see step 3), such as the number of patients unwilling to utilize qOET, is integrated in the economic evaluation. The aim is to establish sustainable financial models for integrating qOET into routine care.

## Step 3: overall evaluation of IMPLEMENT

The assessment of the outcome of IMPLEMENT is primarily guided by the RE-AIM framework. The evaluation builds on the qualitative and quantitative data collected at both baseline and follow-up:

An assessment of RE-AIM categories [18] using a questionnaire completed jointly by the addressee and a researcher for all institutions providing qOET.An individual questionnaire for cancer patients and stakeholders.Qualitative interviews of cancer patients and stakeholders.

Baseline assessments take place prior to the delivery of any initial IPS (November 2023 – February 2024). The follow-up assessment is scheduled for November 2025 – February 2026. Newly participating institutions joining the IMPLEMENT network and those already providing qOET at the time of recruitment will complete the baseline assessment as soon as possible after joining.

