**Methods:**

The IMPLEMENT project is designed as an exploratory study with a quasi-experimental design and a mixed-methods approach, combining qualitative and quantitative data collection. Institutions involved in the treatment and/or aftercare of cancer patients will be approached to identify key barriers and facilitators of qOET. Based on these findings, a set of implementation strategies (IPS) will be developed, implemented, and evaluated to facilitate the delivery of qOET for cancer patients. We aim to develop a variety of IPS for different contexts: urban settings (e.g. qualifying local aftercare institutions to provide qOET); rural settings (e.g. a hybrid approach for areas with limited access to local qOET services); adult cancer patients (e.g. focussing on patient education); and children and young cancer patients (e.g. offering consultations with training therapy experts). Additionally, interface management, training concepts, digital support, and economic evaluation will be considered to further promote the wider dissemination of qOET. The impact of the IPS will primarily be measured by the reach of qOET, assessed by comparing the number of cancer patients receiving qOET before and after implementation.

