With respect to the low number of centres offering qOET and high levels of physical inactivity in adult and paediatric cancer patients, the fragmented landscape highlights the urgent need for national efforts to integrate qOET into routine cancer care in Germany [7, 17]. The evidence supporting qOET for cancer patients, combined with the current lack of its implementation in Germany, forms the overarching rationale for the IMPLEMENT project. IMPLEMENT aims to strengthen the implementation of qOET in cancer patients across Germany by identifying and addressing multiple barriers and facilitators. The project aims are structured around the RE-AIM (Reach, Effectiveness, Adoption, Implementation and Maintenance) framework [18]. The primary outcome of IMPLEMENT is to expand the reach of qOET, specifically by increasing the overall number of cancer patients receiving qOET. Additionally, secondary outcomes have been developed in line with the RE-AIM framework (see additional file 2 for the full list). Key secondary outcomes involve:

Increasing the number of cancer patients reporting a significant positive impact of qOET on their daily life (effectiveness).Expanding the number of institutions offering qOET (adoption).Promoting the qOET professional training programme and increase certification by at least 50% of therapists (implementation consistency).Ensuring the sustainability of implementation options to provide qOET provision beyond the three-year project period through the promotion of funding opportunities (maintenance).

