## Methods

### Design of the project

The IMPLEMENT project is designed as an explorative study with a quasi-experimental design using mixed-methods. The consortium consists of researchers and clinicians from eight university hospitals and research institutions across Germany (the “IMPLEMENT sites”, further details at https://cio.uk-koeln.de/leben-mit-krebs/bewegung/studien-und-publikationen/implement-projekt/). To enhance the implementation of qOET in Germany, IMPLEMENT’s core objective is to iteratively develop, implement, and evaluate various implementation strategies (IPS) over a three-year period. This process involves three key steps. Step 1 focuses on identifying key barriers and facilitators for implementing qOET in various settings, which is conducted at the project’s outset to inform the development of IPS. Step 2 involves the iterative design, implementation, and evaluation of these IPS throughout the three-year period. The IPS are designed by the IMPLEMENT sites (see below for further details) and implemented in the “network” of each IMPLEMENT site. The “networks” of each single IMPLEMENT site potentially include any collaborating institutions and/or stakeholders involved in the treatment of cancer patients, such as clinics, physicians, rehabilitation centres, or physiotherapists. An expansion of the networks is a desired consequence of steps 1 and 2. Finally, step 3 encompasses a comprehensive analysis of qOET implementation in Germany and a process evaluation of the IPS before the end of the funding period. In this step, promising IPS will be disseminated widely to further facilitate the adoption of exercise therapy among cancer patients.

The IMPLEMENT project is divided into five partially overlapping subprojects, each targeting a distinct population or fulfilling a specific role within the overall framework of the project (Fig. 1).

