### Assessment of RE-AIM

All institutions within the IMPLEMENT network involved in the delivery of qOET are assessed using a dedicated questionnaire (see Supplemental file 3 for full questionnaire). This tool collects relevant data to estimate the impact of the IMPLEMENT project with respect to the primary and secondary outcomes (see add file 2):

The RE-AIM categories of Reach, Effectiveness, Adoption, Implementation and Maintenance.Indicators of qOET to ensure that all conditions for providing a qOET are met by the institution.

Each institution is required to report the number of cancer patients who received qOET during a specified three-month period in the previous year, as well as the overall number of cancer patients with a primary diagnosis over the preceding year. Assuming the overall number of cancer patients remains relatively stable from year to year, we aim to calculate the proportion of cancer patients receiving qOET. We anticipate that this proportion will increase due to the specific IPS interventions.

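### Reach is given as both a number and a proportion over a changing, providers-only set of institutions, so the proportion can fall when adoption succeeds

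*Protocol article*

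**What the plan says.** **Measure.** The Abstract (Methods) says that impact is primarily reach, "assessed by comparing the number of cancer patients receiving qOET before and after implementation". The Introduction also words the primary outcome as a count: "specifically by increasing the overall number of cancer patients receiving qOET". Under Assessment of RE-AIM, institutions report their qOET patients in a three-month period and their patients with a primary diagnosis over a year, and "we aim to calculate the proportion of cancer patients receiving qOET". The article adds: "We anticipate that this proportion will increase due to the specific IPS interventions".

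**Who is asked.** Step 3 describes the RE-AIM questionnaire as "completed jointly by the addressee and a researcher for all institutions providing qOET". Assessment of RE-AIM repeats the restriction: "All institutions within the IMPLEMENT network involved in the delivery of qOET are assessed".

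**The set of institutions.** Design of the project says "An expansion of the networks is a desired consequence of steps 1 and 2". Recruitment of collaborating institutions describes inviting further institutions, and the Introduction lists a larger number of institutions offering qOET as a key secondary outcome.

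**Joiners.** Step 3 provides that "Newly participating institutions joining the IMPLEMENT network and those already providing qOET at the time of recruitment will complete the baseline assessment"; this is to happen promptly once they have joined. The main baseline is placed before any initial implementation strategy (IPS) is delivered.

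**The concern.** The article does not say whether the number or the proportion decides the primary outcome, and it ties neither to a defined or matched set of institutions. The data-collection rule makes the proportion conditional on being a provider at that wave. A network institution that provides no qOET at baseline has zero reach, but neither that zero nor its patients enter the baseline figure. By the same wording, an institution that stops would not enter the follow-up figure.

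The project sets out to turn non-providers into providers. If new providers start with lower reach than established ones, success on adoption pulls the pooled proportion down, against the article's own prediction, while the count goes up. If low-reach providers stop, the reverse happens. The direction of the primary result can therefore depend on which version is reported.

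The count has a separate, conditional weakness. Institutions that already provided qOET before joining bring existing patients with them. Whether these look like a gain depends on how the late baselines are used, which the article leaves open.

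**Working it through.** **The article's own figure.** No target, sample size or power is stated for reach. The only such figure, under Recruitment of cancer patients, concerns Likert items in the patient questionnaire: 300 per time point, effect size 0.3, alpha 0.05, power 95%. It reproduces (two-sided, standardised effect): Φ(0.3 × √(300/2) − 1.96) = Φ(1.71) = 95.7%. It has no bearing on reach, so the point is checked by arithmetic on reach itself.

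**Inputs.** The documents give no institution counts. All counts below are assumptions: 1,000 patients per institution, with 20 providers at 30% at baseline, so 6,000 / 20,000 = 30%.

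**Case A: 20 network non-providers start qOET at 10%.**
- New qOET patients: 20 × 1,000 × 10% = 2,000.
- Count: 6,000 to 8,000, and 8,000 / 6,000 = 1.33 (+33%). This is a real gain.
- Providers-only proportion: 6,000 / 20,000 = 30% to 8,000 / 40,000 = 20%.
- Same 40 institutions at both waves: 6,000 / 40,000 = 15% to 8,000 / 40,000 = 20%.

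**Case B: the reverse. Those 20 sites provide at 10% at baseline and stop.**
- Count: 8,000 to 6,000, a fall of 2,000 / 8,000 = 25%.
- Providers-only proportion: 20% to 30%.
- Same 40 institutions: 20% to 15%.

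**Case C: five institutions of the same size, already at 30%, join and nothing changes.**
- Raw totals: 6,000 to 6,000 + 1,500 = 7,500, and 7,500 / 6,000 = 1.25 (+25%).
- With their catch-up baselines in the baseline total: 7,500 to 7,500 (0%).
- Proportion: 30% either way.

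**When does the proportion fall?** The pooled figure drops only if new providers' reach is below the existing average. Take one provider at 300 / 1,000 and one starter with 500 patients:

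| Starter's qOET patients | Providers-only, baseline to follow-up | Both institutions at both waves |
|---|---|---|
| 25 (5%) | 30.0% to 325/1,500 = 21.7% | 20.0% to 21.7% |
| 50 (10%) | 30.0% to 350/1,500 = 23.3% | 20.0% to 23.3% |
| 100 (20%) | 30.0% to 400/1,500 = 26.7% | 20.0% to 26.7% |
| 150 (30%) | 30.0% to 450/1,500 = 30.0% | 20.0% to 30.0% |
| 200 (40%) | 30.0% to 500/1,500 = 33.3% | 20.0% to 33.3% |

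The fixed-set baseline is 300 / 1,500 = 20.0%. Over the fixed set reach rises in every row. The providers-only figure falls in the first three, is flat in the fourth and rises in the last. If the established provider also improves to 330 and the starter reaches 50, the providers-only figure still falls, to 380 / 1,500 = 25.3%.

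**The case against.** A reader might infer that recruiting institutions inflates the count as such. The article does not support that. Step 3 gives joiners, expressly including those already providing qOET, their own baseline, and the questionnaire looks back at a period in the previous year, so a late form can capture patients treated before joining. If that baseline is counted, the 25% in Case C disappears. The article nowhere says that raw totals at the two calendar windows will be compared. Patients at an institution that newly starts qOET are a genuine gain in the count.

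A reader might also infer that institutions that stop are certain to be dropped. That is a consequence of the providers-only wording, not something the article states. The section on serious adverse events has a rule triggered by a decline in the proportion of institutions providing qOET, which presupposes that stoppers are known.

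Other sections collect information on non-providers: the needs assessment in Step 1, the five-level classification of paediatric clinics in SP1a and the facility visits in SP1c. The Step 3 sentence on newly participating institutions can be read as including non-providers. The study is declared exploratory, and pooling rules may sit in an analysis plan.

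These points make the count claim conditional. They do not settle the proportion. None of those other sections says that total patient numbers are collected from non-providers for the reach calculation, and the possible inclusion of non-providers in Step 3 conflicts with the providers-only wording nearby. An analysis plan can choose how to pool, but it cannot supply denominators that were never collected. The catch-up baseline is also only a partial remedy: its role in the comparison is undefined, and it may be completed after IPS delivery has begun.

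**Conclusion.** The point holds in a qualified form. Reach is defined in two ways, and the instrument supplying both is restricted by its wording to current providers in an open network. A pooled providers-only proportion can fall while reach over the same institutions rises (30% to 20% against 15% to 20% in Case A), and can rise when low-reach sites stop; in both cases the count moves the opposite way to the proportion. The effect on the proportion requires new or lost providers to have below-average reach. That is plausible for start-ups but is an assumption, and there is no fall once new providers match the existing average.

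Inflation of the count is conditional: between 0% and 25% in Case C, depending wholly on whether catch-up baselines enter the baseline total. The sizes are illustrative because every institution count is assumed. That the two measures can diverge follows from the arithmetic once institutions are pooled over this changing set.

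**What to change.** 1. Name one primary reach measure, number or proportion, and use it in the Abstract, the Introduction and Assessment of RE-AIM.
2. Collect the two reach items (qOET patients and total patients) from every network institution at both waves. Enter zero qOET patients with the full denominator for non-providers and for institutions that have stopped.
3. Compare each institution with its own baseline. For joiners, use the catch-up baseline with a reference period that ends before joining.
4. Report later joiners on separate lines: those already providing before joining, credited only with change from their own baseline, and those that started after joining, credited as gain.
5. Reconcile the providers-only wording with the Step 3 sentence on newly participating institutions, so that it is clear whether non-providers complete a baseline.

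Restricting the primary comparison to institutions in the network at the first baseline is a further option but is not required. Bringing in new providers is part of what the project does, and paired comparison with separate lines for joiners keeps that gain visible.

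The cost is revised outcome wording, a two-item form for non-providing and stopped institutions, and possibly a less favourable headline increase. If the baseline window has closed, the item still needed for non-providers is their total patient number for the baseline year, since their qOET number is zero.

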**Fig. 1 Fig1:**
[figure not shown]
Structure of the overall IMPLEMENT project and subprojects (SP). AYAs: adolescents and young adults, aged 18–39 years. Adults: aged 40 + years

Subproject1 (SP1) covers all relevant care sectors where qOET can be applied. It is further subdivided into the following components:

SP1a, addressing paediatric and AYA cancer patients.SP1b, addressing adult cancer patients.SP1c, addressing cancer patients living in urban areas.SP1d, addressing cancer patients living in rural areas.SP1e, addressing interfaces and overlaps among SP1a-d.

Subprojects of SP1 as well as the overlapping SP2 (focussing on the education and training of physicians, exercise therapists, clinicians, nurses) are designed to develop, implement, and evaluate IPS to achieve the primary and secondary aims of IMPLEMENT. These IPS include standardised operating procedures (SOPs) with indicators that can be used for process evaluations, to enable other IMPLEMENT sites to run the IPS in their network. SOPs are presented and discussed within a *“Learning System”*, a bi-weekly online meeting of all IMPLEMENT sites (details see below). Once developed, all IMPLEMENT sites are encouraged to implement all IPS that fit to the needs of their networks in the implementation phase, which covers two years of the IMPLEMENT project (see Fig. 2). Subprojects are also responsible for monitoring and evaluating the process of their IPS throughout the implementation phase. SP3 aims to develop digital support for SP1 and SP2, such as web-based resources and social media content. SP4 ensures secure data management structures for all data collected within IMPLEMENT, including the establishment of a REDCap-based database. SP5 is designed to evaluate the overall outcome of IMPLEMENT and to advise on generic IPS that can be utilised in SP1 and SP2.

Ethics approval for IMPLEMENT was initially obtained from the University of Bremen, Germany (ref. 2023-16). All participating institutions received ethics approval from their respective ethics committees based on this initial authorization.

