### SP1c: urban areas

The main goal of SP1c is to increase the number of local institutions, particularly physical therapy facilities, capable of providing qOET to cancer patients. In a first step, local physical therapy facilities are identified through personal contacts and/or a web-based search. If available, the facility’s website is reviewed for information regarding services for cancer patients and relevant billing options. Secondly, information materials outlining the benefits of qOET, current training and education options for health care professionals (see SP2), and details about the IMPLEMENT project are sent to the facility by mail and email. With the facility’s consent, IMPLEMENT staff conduct a personal visit to evaluate which qOET requirements, relating to knowledge, equipment, spatial requirements, staff qualification, and financing, are not being met. Finally, facilities receive tailored support to address the identified gaps until all qOET requirements are fulfilled. If staff qualification is identified as a need, therapists are referred to SP2 for appropriate training. Institutions fulfilling all qOET requirements are encouraged to participate in the referral management processes established under SP1e.

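### Institutions that join after the implementation strategies have started still file a form called baseline, so some of the 'before' values can already contain project effects

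*Protocol article*

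**What the plan says.** Step 3: overall evaluation of IMPLEMENT gives two timing rules for one assessment. The first is: "Baseline assessments take place prior to the delivery of any initial IPS", with the window November 2023 to February 2024. The second covers newly joining institutions, and those already providing qOET when recruited. They "will complete the baseline assessment as soon as possible after joining". For follow-up: "The follow-up assessment is scheduled for November 2025 – February 2026".

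Late joining is expected. Design of the project states: "An expansion of the networks is a desired consequence of steps 1 and 2". The text below Fig. 1 has sites apply the strategies "in the implementation phase, which covers two years of the IMPLEMENT project".

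On who is assessed, Assessment of RE-AIM says: "All institutions within the IMPLEMENT network involved in the delivery of qOET are assessed using a dedicated questionnaire". The same section asks for the number of patients who received qOET in a specified three-month period of the previous year. That is the only look-back over past activity that the article ties to an outcome besides the yearly number of primary diagnoses used as denominator.

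Under SP1c: urban areas, a facility is first identified, then sent material on qOET and on training options, then visited with its consent to find unmet requirements. After that, "facilities receive tailored support to address the identified gaps until all qOET requirements are fulfilled".

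**The concern.** The main result is a before/after comparison, so each 'before' value should describe the institution before the project acted on it. The first timing rule secures this. The second does not: it fixes the form to the joining date, and an institution may join when IPS have been running for many months.

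Several strategies do not wait for an institution to join. SP1c sends its mailing, which includes training options, before the facility has agreed to a visit. SP1b patient materials, SP2 training and the SP3 public platform can also reach a facility from outside the network. A practice that trained staff because of the mailing and joined afterwards would report those trained therapists at baseline. Joining may itself be an effect of the strategies, so late joiners are not a random subset.

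At stake are reach (primary outcome) and two key secondary outcomes: the number of institutions offering qOET and therapist certification. If late forms are pooled with the first wave, part of the estimated change depends on when a form was filled in.

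**Working it through.** **The plan's own figure.** The article gives no number for late joiners or for the effect of their timing. Its only power statement (300 patients per time point, effect 0.3, alpha 0.05, power 95%) concerns the patient questionnaire. It reproduces as 95.7% (two-sided, SD taken as 1) and has no bearing here.

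**1. Can both timing rules hold?** For an institution joining by February 2024, yes. For one joining later, the form cannot fall in the stated window and falls after IPS have started in the project. Between the end of the baseline window and the start of follow-up lie March to December 2024 (10 months) and January to October 2025 (10 months), 20 months in all. Nothing in the text stops a baseline form being filed in any of them.

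**2. Does the look-back protect the patient count?** Assumption: IPS start on 1 March 2024, when the baseline window has closed. The table counts how many of the 12 look-back months fall after that date.

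| Joining month | Previous calendar year | Preceding 12 months |
|---|---|---|
| March 2024 | 0 | 0 |
| June 2024 | 0 | 3 |
| September 2024 | 0 | 6 |
| December 2024 | 0 | 9 |
| January 2025 | 10 | 10 |
| March 2025 and later | 10 | 12 |

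For a January 2025 joiner, 12 − 10 = 2 months precede IPS start on either reading. For later joiners at most 2 do. No three-month period in that look-back can then lie wholly before IPS. For 2024 joiners the calendar-year reading protects fully. On the rolling reading, protection depends on which three months are specified. If the questionnaire names one fixed calendar period for all institutions, whatever their joining date, reach is protected throughout; the article does not say so.

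**3. Adoption and training.** The article states no look-back for qOET status or therapist training. On its text alone, these items describe the day the form is completed.

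**4. Size.** Let s be the late joiners' share of patients and f the share of the gain already present when they file. With the same true gain everywhere and late forms pooled as baseline:

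observed gain = true gain × (1 − s × f)

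For a true gain of 10 percentage points (s and f assumed):

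- f = 0, any s: 10.0
- s = 0.1, f = 0.5: 10 × (1 − 0.05) = 9.5
- s = 0.3, f = 0.5: 10 × (1 − 0.15) = 8.5
- s = 0.3, f = 1: 10 × (1 − 0.30) = 7.0
- s = 0.5, f = 1: 10 × (1 − 0.50) = 5.0

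The article gives neither s nor f, so this shows direction and sensitivity and is not an estimate.

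**The case against.** The strongest reply is that rolling entry with a baseline at entry is normal where a network is meant to grow. On this view the first rule describes the main wave and the second serves those who could not be in it. The late form is also tied to joining and is to be done promptly, so it may well precede the institution's own support. SP1c records unmet requirements at a visit before tailored support, and SP1a classifies each paediatric clinic at baseline before strategies are tailored to it. The RE-AIM questionnaire and the outcome list are in supplementary files not shown here, and the outcomes belong to an exploratory study.

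Much of this stands. It rules out a stronger reading that a reader might infer: that because the RE-AIM questionnaire is addressed to institutions delivering qOET, a facility converted by SP1c files its first form only after conversion, so that its gain always disappears and the adoption change could shrink to nothing. The documents do not support this. The trigger is joining, not qualifying. The timing rule lists institutions already providing qOET alongside newly joining ones, so non-providers can be read as included. Recruitment of collaborating institutions does not require current qOET delivery either.

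The reply does not remove the narrower point. Prompt completion after joining is not completion before IPS contact, since the mailing, training and platform can come first. The SP1c visit captures the state before tailored support, but it follows the mailing. The look-back does not secure a pre-IPS count for institutions joining well into the implementation phase. The article sets no rule that keeps late forms apart from true pre-IPS forms.

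**Conclusion.** The concern holds in limited form. For institutions joining after February 2024, the article calls a form baseline that does not meet its own definition of baseline. Such forms can already contain project effects on adoption and therapist training. For institutions joining about a year or more after IPS start, this extends to the reach count (from January 2025 under the assumed start of 1 March 2024).

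If IPS increase provision and late forms are pooled with the first wave, the bias understates the change. Its size cannot be computed from the article. It is zero if late joiners were untouched by IPS when they filed, or if the unseen questionnaire ties its items to a fixed pre-IPS period. It grows with the late joiners' share and with how much of their gain came first. The two timing rules should be reconciled before the follow-up data are analysed.

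**What to change.** - Reserve the term baseline for one fixed reference period before the first IPS, named by calendar date, and label forms completed on later joining as entry forms.
- For each late joiner, record three values for that fixed period: whether the qOET conditions were met, the number of OTT-trained therapists, and the three-month patient count.
- Use the SP1c visit record or the SP1a baseline classification for the pre-support state where one exists, and retrospective items otherwise. Where IPS contact came before the visit or classification, still ask for the fixed-period values.
- Store the joining date and the date of first IPS contact in REDCap.
- Report late joiners separately from institutions with a true pre-IPS baseline, and do not pool entry values with baseline values.

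The cost is a few extra fields, a wording change and some recall error in the retrospective items, which grows with the delay between the reference period and joining.
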